# Treatment of voluminous and complicated superficial slow-flow vascular malformations with sirolimus (PERFORMUS): protocol for a multicenter phase 2 trial with a randomized observational-phase design

**DOI:** 10.1186/s13063-018-2725-1

**Published:** 2018-06-27

**Keywords:** Vascular anomalies, Lymphatic malformations, Venous malformations, Children, Sirolimus, Mammalian target of rapamycin inhibitors, Randomized placebo-phase design

## Abstract

**Background:**

Slow-flow superficial vascular malformations (VMs) are rare congenital anomalies that can be responsible for pain and functional impairment. Currently, we have no guidelines for their management, which can involve physical bandages, sclerotherapy, surgery, anti-inflammatory or anti-coagulation drugs or no treatment. The natural history is progressive and worsening. Mammalian target of rapamycin (mTOR) is a serine/threonine kinase that acts as a master switch in cell proliferation, apoptosis, metabolism and angio/lymphangiogenesis. Sirolimus directly inhibits the mTOR pathway, thereby inhibiting cell proliferation and angio/lymphangiogenesis. Case reports and series have reported successful use of sirolimus in children with different types of vascular anomalies, with heterogeneous outcomes.

**Objective:**

The objective of this trial is to evaluate the efficacy and safety of sirolimus in children with complicated superficial slow-flow VMs.

**Methods/design:**

This French multicenter randomized observational-phase, phase 2 trial aims to include 50 pediatric patients 6 to 18 years old who have slow-flow (lymphatic, venous or lymphatico-venous) voluminous complicated superficial VM. Patients will be followed up for 12 months. All patients will start with an observational period (no treatment). Then at a time randomly selected between month 4 and month 8, they will switch to the experimental period (switch time), when they will receive sirolimus until month 12. Each child will undergo MRI 3 times: at baseline, at the switch time, and at month 12. For both periods (observational and treatment), we will calculate the relative change in volume of the VM divided by the study period duration. This relative change weighted by the study period duration will constitute the primary endpoint. VM will be measured by MRI images, which will be centralized and interpreted by the same radiologist who will be blinded to the study period. Hence, each patient will be his/her own control. Secondary outcomes will include assessment of safety and efficacy by viewing standardized digital photographs and according to the physician, the patient or proxy; impact on quality of life; and evolution of biological makers (coagulation factors, vascular endothelial growth factor, tissue factor).

**Discussion:**

The main benefit of the study will be to resolve uncertainty concerning the efficacy of sirolimus in reducing the volume of VMs and limiting related complications and the safety of the drug in children with slow-flow VMs. This trial design is interesting in these rare conditions because all included patients will have the opportunity to receive the drug and the physician can maintain it after the end of the protocol if is found efficient (which would not be the case in a classical cross-over study).

**Trial registration:**

ClinicalTrials.gov Identifier: NCT02509468, first received: 28 July 2015.

EU Clinical Trials Register EudraCT Number: 2015-001096-43.

**Electronic supplementary material:**

The online version of this article (10.1186/s13063-018-2725-1) contains supplementary material, which is available to authorized users.

## Background

### Background and rationale

Vascular anomalies (VAs) include a heterogeneous group of disorders occurring most frequently in newborns and children. Infantile hemangiomas are common (10% of infants), are generally not complicated and are easily managed, but most other VAs are rare (< 2% altogether) and we have no guidelines for management.

The updated classification from the International Society for the Study of Vascular Anomalies (ISSVA), divides VAs into 2 broad categories: vascular tumors and vascular malformations (VMs) [1]. VMs are usually present at birth, although they are not always apparent at this stage; they are distinguished by their hemodynamic flow as high-flow and slow-flow VMs. Slow-flow VMs involve abnormal capillaries vessels (i.e., port-wine stains), venous vessels, lymphatic vessels (including macrocystic, microcystic or mixed lymphatic malformations) or a combination of these. They can be superficial (involving cutaneous and subcutaneous tissues, underlying fasciae and muscles) or may have visceral involvement. They can be limited or diffuse and are sometimes components of genetic syndromes (e.g., Protée, Klippel-Trenaunay, Bean syndrome) [2]. They are always due to defective embryologic vasculogenesis [3]. Slow-flow VMs are diagnosed on physical examination, but a biopsy might be required for confirmation. Diagnosis is always completed with imaging, including duplex ultrasonography for screening, and MRI for definitive diagnosis and diagnosis of extension [4]. Recent molecular findings have allowed for a better understanding of VMs, in particular those for which somatic mutations of genes were identified, especially *PIK3CA*, causing overgrowth tissue associated with the VM [5, 6]. Slow-flow superficial VMs might induce functional impairment because they can be voluminous, painful, associated with underlying overgrowth tissue, or complicated by seepage or continuous cutaneous bleeding. Visceral VMs can be life-threatening when complicated by gastrointestinal bleeding, for instance, or hematologic disturbances (anemia, thrombopenia).

Management of slow-flow VMs requires dedicated multispecialty care. We have no guidelines for treatment, and management may include no intervention (although the natural history of these VMs is progressive worsening), compression with a physical bandage, sclerotherapy, resection (when feasible), anti-inflammatory or anti-coagulation drugs, or interferon or anti-proliferative drugs [7, 8]. Literature reporting medical therapies for slow-flow superficial VMs consists mainly of pediatric case reports and features publication bias, inconsistent use of nomenclature and lack of clinical trials.

Mammalian target of rapamycin (mTOR) inhibitors, usually indicated as immunosuppressive agents for preventing organ rejection [9], have been recently used for VAs, given their anti-proliferative and anti-angio/lymphangiogenic properties, with very promising results [9–12]. They directly inhibit mTOR, a serine-threonine kinase regulated by phosphoinositide-3-kinase (PIK3), which acts as a master switch in numerous cellular processes such as cell growth and proliferation, cellular metabolism, autophagy, and angio/lymphangiogenesis. Inhibitors of mTOR were found efficient in several cases of VAs [12, 13]. A systematic review recorded 84 cases of VAs treated with mTOR inhibitors up to 2014 [14].

Sirolimus (or rapamycin), which has the advantage of oral administration, was the most frequently used mTOR inhibitor and had quick efficacy in children with slow-flow VMs, with overall good tolerance. However, the sirolimus doses, monitoring and outcomes were heterogeneous. An observational study of 61 cases published since then showed more mitigated results [15]. All authors highlighted the need to perform randomized clinical trials to better delineate sirolimus indications in VMs and the modalities of posology and monitoring.

### Objectives

We aimed to perform a clinical trial (*suPERficial slow-flow vascular malFORMations treated with sirolimUS;* PERFORMUS) to assess the efficacy and safety of sirolimus in complicated slow-flow VMs in children.

### Trial design

PERFORMUS is a multicentre phase 2 trial with a randomized observational-phase design derived from the design described by Feldman et al. [16]. Patients will be followed up for a total of 12 months. All will start with an observational period (no treatment), then will switch to an experimental period, when they will receive sirolimus. The switch time will be randomized, ranging from month 4 to month 8 (Fig. 1). Such a design was preferred to a two-parallel group design because it allows all children to receive treatment at some time point, thus encouraging physician adherence to the protocol and better patient acceptance. As well, it provides greater power as compared with a two-independent group trial.

**Fig. 1 Fig1:**
[figure not shown]
The randomized observational-phase design: data collection for the primary outcome, from MRI

## Methods: participants, interventions, and outcomes

### Study setting

The study will be conducted in 12 French tertiary hospital centers involving multidisciplinary consultations (with dermatologists, radiologists and surgeons) dedicated to VAs.

### Eligibility criteria

#### Inclusion criteria

Pediatric patients, age 6 to 18 years, with complicated superficial slow-flow VM extending to underlying tissues (subcutaneous tissue, fasciae, muscles and/or bones) and confirmed by MRI will be eligible. The minimum age of 6 years was chosen to avoid repeated MRI under sedation, as is commonly used for children < 6 years old in most French radiologic centres. Any type of slow-flow VMs, belonging or not to a genetic disorder, might be included, except for pure macrocystic lymphatic malformations, for which sclerotherapy is the usual treatment. Therefore, patients with microcystic lymphatic VMs, mixed micro- and macrocystic VMs, venous malformations or combined lymphatic and venous malformations are eligible if the VM is complicated. Complications might be linked to the volume, pain, functional impairment, bleeding and/or seepage.

#### Exclusion criteria

Patients with life-threatening VM due to complicated visceral involvement will be excluded, as will patients with immunosuppression, a chronic infectious disease or history of cancer in the 2 previous years, contraindications to MRI (prosthesis), pregnancy, and females of childbearing age not using birth control. We will exclude patients with contraindications to sirolimus: allergy to mTOR inhibitor or lidocaine, allergy to peanuts or soybean (only sirolimus pills will be allowed), concomitant treatment that interferes with CYP3A4, concomitant immunosuppressive treatment or previously received an mTOR inhibitor, intolerance to fructose, intolerance or malabsorption to glucose or galactose, metabolic insufficiency in sucrase-isomaltase, metabolic defect in lactase, and liver insufficiency (elevated transaminase level > 2.5 N), anemia (hemoglobulin level < 9 g/dl), leukopenia (white blood cell count < 1000/mm^3^), thrombocytopenia (platelet count < 80,000/mm^3^), or hypercholesterolemia (low-density lipoprotein-cholesterol level ≥ 2 g/l).

### Intervention

Sirolimus will be administered in oral suspension or tablets according to the patient’s age, starting with 0.08 mg/kg/day, max 2 mg/day, twice a day, with dose adjustments based on serum level of sirolimus at day 15 to reach target levels 4 to 12 ng/ml. The maximum dosage will be 6 mg per day. A pharmakocinetics model was developed for sirolimus dose adjustment and was made available for investigators via a secured website (https://pharmaco.chu-limoges.fr/). The model allows for describing and predicting the evolution of drug concentrations based on individual information (measured sirolimus trough level, dose administered and patient weight) and on an a priori set of pharmacokinetics parameters (= the pharmacokinetics population model).

Sirolimus will be supplied to pharmacists at each investigational site and will be in charge of the traceability and storage. The products will be stored at room temperature (maximum 25 °C) for the tablet form and in a cool place (2 to 8 °C) for the oral suspension.

Regarding concomitant treatments, all will be allowed, except for drugs that inhibit CYP3A4 (ketoconazole, voriconazole, itraconazole, telithromycin, clarithromycin) or activate it (rifampcin, rifabutin); and for other concomitant immunosuppressive drugs (to minimize risks of infection).

### Outcomes

#### Primary outcome

The primary outcome is based on the volume of the VM seen on MRI. Patients will undergo 3 MRIs: one at baseline (M0), one at the time of switch from the observational period to the sirolimus period (MS, for “month of switch”) and one at the end of follow-up (M12) (Fig. 1). Relative change in VM volume, divided by the duration period, will define the outcome. Thus, for the observational period, the primary outcome is defined as {(VMS – V0)/V0}/(MS-M0), where V0 and VMS are the volumes assessed at baseline and month S respectively, and (MS-M0) is the duration of the observational period. For the sirolimus period, the outcome is defined in the same way: {(V12 – VMS)/VMS}/(M12-MS), where V12 is the volume assessed at month 12 when the study ends, and (M12-MS) is the duration of the sirolimus period.

### Secondary outcomes

Secondary outcomes are clinical and biological assessments of the efficacy of sirolimus as well as safety.

Clinical efficacy will be assessed by different endpoints (Table 1).

**Table 1 Tab1:** Schedule of study interventions, outcome data collection and follow-up visits

	Screening	Inclusion	Switch (start sirolimus)	Switch + M1 ± 15 days	Follow-up during sirolimus treatment: every 2 months ±15 days	End of study
	J-30/J0*	J0	Between month 4 and 8**	Between month 5 and 9**	Between month 7 and 11**	Month 12***
Information	x	x				
Inclusion/exclusion criteria	x	x	x	x	x	
Medical history and demographics	x	x				
Consent		x				
Randomization		x				
MRI	x^1^		x			x
Physical examination		x	x	x	x	x
General laboratory tests		x^2^	x^3^	x^4^	x^4^	
Coagulation markers, serum VEGF, tissue factor		x		x	x	x
Serum level of sirolimus adjustments^5^				x	x	
Blood and skin samples for genetic analysis and collection (ancillary study)		x				
Photographs		x	x			x
Self-assessment for patients and proxy by visual analog scale			x	x	x	x
Dermatological quality of life scale		x	x	x	x	x
Adverse events/serious adverse events^6^				x	x	x

*possibly by call phone

**depending on the date of the treatment switch from observational to treatment stage

***sirolimus might be maintained at the discretion of investigators after the protocol is finished

^1^included in routine care

^2^complete blood count, ionogram, creatinine, urea, liver enzymes (gamma-GT, SGOT, SGPT), cholesterol, triglycerides, glucose, infection with HIV and hepatitis B and C, serum β-hCG or urine pregnancy test for women of childbearing age

^3^complete blood count, ionogram, creatinine, urea, liver enzymes, cholesterol, triglycerides, glucose, urinary pregnancy test on women of childbearing age

^4^every month during sirolimus: complete blood count, ionogram, creatinine, urea, liver enzymes, cholesterol, triglycerides, glucose

^5^performed after 15 days of sirolimus and then once a month

^6^adverse events will be recorded from when the informed consent form is signed

*VEGF* vascular endothelial growth factor

Two blinded independent trained readers will qualitatively assess digital photographs. For each patient, readers will be provided photographs at baseline and those at MS and M12 without informative data; they will be asked to identify which photograph was taken at the end of the observational period and which at the end of the sirolimus period. Such a procedure represents a “lady-tasting-tea” procedure [17]. Guidelines will be given to the investigators to perform, with their own camera, a front, a profile and a ¾ photograph of the VM at a 50 cm-distance, with a decimeter placed beside the malformation, the child being standing up or lying. They will be asked to send a copy of the photographs to the Clinical Investigation Center of Tours for further centralized assessment. The photographs will be previously registered with initials of the names, code of the center and inclusion number.

Clinical global improvement will be assessed by an unblinded physician on a 0–10 visual analog scale and will be self-assessed by the patient or proxy (parents) on a 0–10 visual analog scale.

Impact on complications will be self-assessed by the patient or proxy, considering pain and skin complications/symptoms (seepage, bleeding, skin tension, functional impairment) and quality of life by the dermatological quality-of-life scale (DLQI) and DLQI adapted for children (C-DLQI) [18].

Biologic markers of efficacy will include coagulation explorations (platelet count, fibrinogen level, D-dimers, factor V levels), supporting the presence and disappearance of an abnormal intravascular coagulation consumption, and plasma levels of vascular endothelial growth factor (VEGF) and tissue factor. VEGF is a major angiogenic factor that stimulates the proliferation and migration of endothelial cells. Strong expression of VEGF has been found associated with VAs, and a few reports have shown changes in serum levels of VEGF after efficient treatment for VAs and different vascularized cancers [19, 20]. Moreover, Medici et al. demonstrated that sirolimus in vitro inhibits the proliferation of hemangioma endothelial cells by reducing the expression of VEGF [21]. Hence, VEGF could be a useful biologic marker for treatment monitoring. In addition, tissue factor, a 47-kDa glycoprotein that is the physiological trigger of blood coagulation, probably has a key role in modulation of angiogenesis, particularly by regulating VEGF expression [22, 23].

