### Statistical methods

Considering the primary outcome, relative changes in volume of VMs will be compared by paired *t* test or Wilcoxon signed-rank test if necessary. For secondary outcomes, physician assessment of efficacy, patient self-assessment and biological relative changes will be analyzed by the same approach (i.e., paired *t* test or Wilcoxon signed-rank test). Considering efficacy on digital photographs, assessed by 2 independent trained readers, the “lady-tasting-tea” procedure will be used to test whether readers performed better than expected in identifying the digital photographs taken after the end of the sirolimus period [17]. Regarding AEs, descriptive statistics (percentages) will be estimated. The ancillary study on genetic samples will be descriptive.

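### Five of the six biological efficacy markers have no scheduled sample at the switch, so on the natural reading of the analysis plan their two-period comparison cannot be formed

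*Protocol article*

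**What the plan says.** The Secondary outcomes section names six biological markers of efficacy: "coagulation explorations (platelet count, fibrinogen level, D-dimers, factor V levels", together with VEGF and tissue factor. Table 1 schedules them in one row, "Coagulation markers, serum VEGF, tissue factor". That row is filled at inclusion, switch plus one month, follow-up and end of study. The screening and switch cells are empty.

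Under Statistical methods, the primary analysis is given first: "relative changes in volume of VMs will be compared by paired" *t* test, or by signed-rank test if needed. The secondary outcomes follow: "physician assessment of efficacy, patient self-assessment and biological relative changes will be analyzed by the same approach", with the same two tests in brackets.

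The Primary outcome section defines the quantity being compared. The observational term is built from two volumes, "where V0 and VMS are the volumes assessed at baseline and month S respectively". Of the second term it says: "For the sirolimus period, the outcome is defined in the same way", this time from the switch to month 12. Each relative change is divided by the length of its period.

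**The concern.** The value at the switch does double duty in this design. It closes the untreated period and is the baseline of the treated one. If a marker is not measured there, neither period has a change and there is nothing to pair.

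What is at stake is the own-control comparison for the biological endpoints. The Background describes the untreated course of these malformations as one of worsening, so drift during the untreated months cannot be assumed to be zero. A change measured across both periods cannot separate that drift from a drug effect. A blood sample that was never drawn cannot be supplied later by an analysis plan.

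**Working it through.** The protocol gives no figure for the marker analysis, so the check sets the schedule against the formula. The article's only power figure concerns the primary outcome. It reproduces (200 × (1 − 0.5)/2 = 50 children) and is untouched by this point.

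**1. Which cells are filled in Table 1**

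| Row | Screening | Inclusion | Switch | Switch + 1 month | Follow-up | Month 12 |
|---|---|---|---|---|---|---|
| Coagulation, VEGF, tissue factor | – | x | – | x | x | x |
| General laboratory tests | – | x | x | x | x | – |
| MRI | x | – | x | – | – | x |
| Photographs | – | x | x | – | – | x |
| Quality of life | – | x | x | x | x | x |

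All five rows have six cells. The general laboratory row also lines up with its footnotes: the panel with the pre-treatment pregnancy test falls at the switch, and the on-treatment panel falls in the two columns after it. The blank is therefore unlikely to come from the conversion of the table.

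**2. Whether another part of the article supplies the value**

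Table 1 footnote 3, the switch panel, lists a complete blood count, routine chemistry, lipids, glucose and a pregnancy test. The Safety section lists similar tests before sirolimus starts. Neither contains fibrinogen, D-dimers, factor V, VEGF or tissue factor. The blood count does give platelets. So 1 of the 6 markers has values at inclusion, switch and month 12, and 6 − 1 = 5 do not.

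**3. What the comparison needs**

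Write X0, XS and X12 for a marker at inclusion, switch and month 12, and S for the switch month. Following the primary outcome:

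- observational term = {(XS − X0)/X0}/S
- sirolimus term = {(X12 − XS)/XS}/(12 − S)

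XS enters both terms. Without it neither exists, so for the five markers 0 of the 50 planned children contribute a pair to this comparison.

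**4. What remains**

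X12/X0 can be computed. It equals (XS/X0) × (X12/XS). Only the product is observed, so any split between the untreated and treated periods is compatible with the data. With S randomised over months 4 to 8, the interval holds between 4 untreated and 8 treated months (S = 4) and 8 untreated and 4 treated months (S = 8).

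**5. Why the sample one month after the switch is no substitute**

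If it closed the first period, one month on drug would fall in an interval of S + 1 months, and the treated interval would shrink from 12 − S to 11 − S months.

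| Switch month | Share of first interval on drug, 1/(S + 1) | Treated interval left |
|---|---|---|
| 4 | 1/5 = 20.0% | 7 of 8 months |
| 5 | 1/6 = 16.7% | 6 of 7 months |
| 6 | 1/7 = 14.3% | 5 of 6 months |
| 7 | 1/8 = 12.5% | 4 of 5 months |
| 8 | 1/9 = 11.1% | 3 of 4 months |

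An early drug effect would be credited to the observational period and removed from the sirolimus period.

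**The case against.** The strongest reply is that Statistical methods borrows only the test. The bracket after the phrase names the paired *t* and signed-rank tests, and the per-period formula is written for MRI volume alone. On that reading, month 12 against inclusion can be computed for all six markers. The same sentence also covers patient self-assessment, whose visual analogue scale has no inclusion value in Table 1.

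Part of this stands. The article never writes the two-period formula for the markers, so the finding is conditional on that reading. A reader might infer that the markers cannot be analysed at all, or that the whole coagulation panel is missing at the switch. The documents support neither: a change from inclusion exists, and platelets are counted at the switch.

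The rest is weaker. A paired test of relative changes, by the approach used for the primary outcome, most naturally means one change per period. The self-assessment example does not help, because improvement ratings at the switch and at month 12 can be paired directly. The test-only reading also gives up the own-control comparison on which the design rests.

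Three further limits should be granted:

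- The article does not propose using the sample one month after the switch in place of a switch value. That harm arises only if someone improvises.
- The full protocol and the SPIRIT figure are not shown, and Table 1 is not flawless: its adverse-event row starts one month after the switch, while footnote 6 starts recording at consent. The blank may be a drafting omission, so it is not established that no child has a switch sample.
- The Discussion singles out clinical efficacy and self-assessed symptoms as the secondary outcomes that matter most, not the biomarkers.

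**Conclusion.** The point holds for five of the six named markers. As scheduled, fibrinogen, D-dimers, factor V, VEGF and tissue factor have no value at the switch, and the two-period paired comparison that the analysis text most naturally describes cannot be formed for them. Within a child, only an uncontrolled change from inclusion is available.

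This rests on two assumptions: that Table 1 reflects the schedule actually followed, and that the same approach means one relative change per period.

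The issue should be fixed, but it is confined to a supportive family of secondary endpoints. A reader might infer that the trial's main result is weakened. It is not: MRI is scheduled at the switch, and the sample size, the primary comparison and the safety monitoring do not depend on these markers.

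**What to change.** Mark the switch cell in this row of Table 1. For every child not yet switched, draw the marker tubes with the blood already taken at that visit, before the first sirolimus dose. State under Statistical methods that the two marker changes run from inclusion to switch and from switch to month 12, each divided by its period length as for volume. State also that the sample one month after the switch does not serve as the end of the observational period.

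For children already switched without a sample, restate the marker analysis as an uncontrolled change from inclusion to month 12. Label it so, and do not present it as evidence of a sirolimus effect against the observational period. Report any two-period analysis in the sampled children as exploratory, since late enrolment or a late switch decides who is in that subset.

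The cost is one extra set of tubes and assays per child at an existing draw. The gain depends on timing. Recruitment was expected to end in March 2018 and the article appeared on 27 June 2018. With switches at months 4 to 8, the last children enrolled would switch between July and November 2018. On that timetable, every child included before 27 October 2017 (8 months before publication) would already have switched. An amendment at publication would therefore reach only part of the cohort, and the restated analysis is needed in any case.

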## Discussion

A randomized trial on sirolimus in VMs was needed, but we had to overcome several difficulties to design such a study: the population is too rare to allow for a parallel-group trial; we have no gold standard for comparing sirolimus; and a placebo group allowing for blinding is not acceptable in this pediatric population because biological samples are required for sirolimus monitoring.

The “randomized observational-phase design” is adapted from the “randomized-placebo phase design” published by Feldman, developed to suit rare conditions for which a placebo group is difficult to obtain. Hence, the design is particularly adapted to rare pediatric conditions. In this design, the subject is his/her own control, as in cross-over trials. However, a cross-over design would have involved the group of patients who receive sirolimus in the first phase to stop it in the second phase, even if it was beneficial. Moreover, cross-over design supposes that after the end of each treatment period, the disease returns to the initial state, which is perhaps not the case here, in that sirolimus might offer lasting improvement.

This randomized observational-phase trial also allows for maintaining sirolimus after the 12-month period of the trial if it is efficient. One of its potential drawbacks is premature termination of treatment. In case this happens, a final assessment (an MRI in our example) will have to be performed.

Because patients and care providers are not blinded to the treatment during that period, the primary outcome was chosen to be as objective as possible (i.e., changes in the volume of the VM seen on MRI). However, in practice, patients complain more about symptoms and complications linked to the VM, such as pain, oozing, bleeding, or functional impairment, than about the volume of the VM. Therefore, assessment of clinical efficacy and self-assessment on symptoms and complications are secondary outcomes of high importance. Safety data will be a focus in this pediatric phase 2 trial, because decisions for treatment in other children with VMs will be based on the benefit/risk ratio.

Hence, the main benefit of the study will be to resolve uncertainty concerning the efficacy and safety of sirolimus in children with slow-flow VMs, a subgroup of VAs that includes heterogeneous entities. If we demonstrate a benefit of sirolimus, the remaining question will be how long treatment has to be maintained.

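### Self-assessed symptoms and complications have no scheduled value before Switch, so scored as levels they have no observational-period change to set against the sirolimus period

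*Protocol article*

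**What the plan says.** All references are to the protocol article.

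- **Schedule (Secondary outcomes, Table 1).** The row "Self-assessment for patients and proxy by visual analog scale" is marked at Switch, Switch + M1, the two-monthly follow-up visits and the end of study. It is blank at Screening and Inclusion. The next row, "Dermatological quality of life scale", is marked at Inclusion and at every later visit.
- **Global rating (Secondary outcomes).** Clinical global improvement is rated by an unblinded physician and "will be self-assessed by the patient or proxy (parents) on a 0–10 visual analog scale".
- **Symptoms (Secondary outcomes).** A separate paragraph states: "Impact on complications will be self-assessed by the patient or proxy, considering pain and skin complications/symptoms". It lists seepage, bleeding, skin tension and functional impairment, and then quality of life by a named scale. No scale is named for the symptoms, and Table 1 has no row labelled for them.
- **Analysis (Statistical methods).** "physician assessment of efficacy, patient self-assessment and biological relative changes will be analyzed by the same approach" as the primary outcome, that is, by paired t test or Wilcoxon signed-rank test.
- **Weight (Discussion).** Because patients complain more of symptoms than of volume, "assessment of clinical efficacy and self-assessment on symptoms and complications are secondary outcomes of high importance".

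**The concern.** The design rests on each child serving as his or her own control. The primary outcome shows what that takes: a value at the start, at Switch and at month 12, giving one untreated change and one change on drug. The symptom self-assessments have only the last two points on the published schedule.

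Pain, oozing, bleeding and functional impairment are most naturally scored as current states. With a first score at Switch, the only pair available is Switch against month 12, entirely on open-label drug. Time trend, expectation and drug effect then sit in one number. At stake is the controlled reading of outcomes that the protocol itself ranks highly. The primary result is not at stake.

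**Working it through.** **1. The plan's own figure.** Sample size gives 50 patients, a correlation of 0.5 between periods, an effect size of 0.4, two-sided 5% and 80% power, said to equal a 200-patient parallel trial.
- Equivalent size per arm = n/(1 − ρ) = 50/(1 − 0.5) = 100, so 200 in total.
- Power with 100 per arm at 0.4 SD: 0.807 (normal approximation). Exact paired t test with 50 pairs: 0.792.

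The stated figure reproduces, and the present point does not touch it.

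**2. Which changes Table 1 allows.** An observational-period change needs a value at Screening or Inclusion and one at Switch. A sirolimus-period change needs Switch and month 12.

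| Row | Before Switch | Switch | Month 12 | Observational change | Sirolimus change |
|---|---|---|---|---|---|
| MRI | yes (Screening) | yes | yes | yes | yes |
| Photographs | yes (Inclusion) | yes | yes | yes | yes |
| Quality-of-life scale | yes (Inclusion) | yes | yes | yes | yes |
| Patient/proxy VAS, read as a level | no | yes | yes | **no** | yes |

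Neighbouring rows keep their Inclusion marks, so the blank does not look like a table broken in extraction.

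**3. What a Switch-to-month-12 test picks up.** This is an illustration on assumed inputs: score SD 1, correlation 0.5 between visits, no drug effect, and a steady drift of b SD per month. Switch months 4, 5, 6, 7 and 8 leave 8, 7, 6, 5 and 4 months on drug, mean 6. The calculation uses 6 months for every patient.
- SD of the paired difference = √(2 × (1 − 0.5)) = 1.
- Mean difference = 6b. Noncentrality = 6b × √50, with 49 degrees of freedom, two-sided 5%.

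| Drift b (SD per month) | Mean difference 6b | Noncentrality | Rejection rate |
|---|---|---|---|
| 0 | 0 | 0 | 5% |
| 0.02 | 0.12 | 0.85 | 13% |
| 0.04 | 0.24 | 1.70 | 38% |
| 0.06 | 0.36 | 2.55 | 70% |

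The sign of b sets the direction of the error. Improvement over time would mimic benefit; worsening would hide benefit or mimic harm.

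**4. What an Inclusion value would restore.** Under the same drift, the change on drug is b(12 − MS) and the untreated change is b × MS. Their raw difference is b(12 − 2MS), which runs from +4b at MS = 4 to −4b at MS = 8. Divided by period length, the two are b and b, and the difference is zero for every patient. The contrast should therefore be per month, as the primary outcome is.

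**The case against.** **The only patient/proxy VAS that the article defines is a rating of improvement.** Improvement cannot be rated on the day of inclusion, so a first mark at Switch is what one would expect. The Switch rating can stand for the observational period and the month-12 rating for the sirolimus period, and a paired test can use the two. This stands for the global rating, provided recall is limited to each period, which the article does not say. A reader might infer from the blank cell that every patient-reported outcome lacks a controlled contrast in all 50 children. The documents do not support that.

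**The symptoms may not belong to the VAS row.** The article names no instrument for them, and the full protocol or case report form may do so. If they were collected on a form used at Inclusion, the gap would close. This limits certainty. However, Data collection methods points to Table 1 as the schedule, and on that schedule only the VAS and quality-of-life rows carry self-report. The text ties the quality-of-life scale to quality of life, listed after the symptoms.

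**Statistical methods names a test and does not promise change against change.** True, so there is no outright contradiction. But a paired test needs two values, and for symptom levels the pair on offer is a pre-post one.

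**The bias need not favour sirolimus.** This stands. The Background says that these malformations tend to worsen, so drift could work against the drug. Regression to the mean after enrolment would act largely before Switch. A reader might infer that spontaneous change is credited in full to sirolimus; the documents do not support that. What remains is that the comparison cannot separate drug from time in either direction.

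**An Inclusion score would not cure expectation bias.** This also stands, because the trial is open-label and expectation enters at Switch regardless.

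**Conclusion.** The point holds for self-assessed pain, seepage, bleeding, skin tension and functional impairment, scored as current levels and collected as Table 1 shows. For these there is no observational-period change, and the planned analysis reduces to an uncontrolled Switch-to-month-12 comparison. The size cannot be fixed from the documents, which give no drift or variance for the symptom scores; the 13% to 70% range shows sensitivity under stated assumptions and is not an estimate.

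The global-improvement VAS, quality of life, photographs and the MRI endpoint are not affected in this way, and the sample size stands. The conclusion rests on two assumptions: that the symptoms are scored as levels, and that no form outside Table 1 collects them at Inclusion. If they are instead rated as improvement, the need is to name the instrument and its recall period. It is a secondary-outcome matter, worth correcting because the protocol ranks these outcomes highly and the remedy is cheap.

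**What to change.** 1. Collect the patient/proxy symptom scores at the Inclusion visit for children still to be enrolled, and mark this in Table 1.
2. Within patient, compare (month 12 − Switch)/(12 − MS) with (Switch − Inclusion)/MS. Absolute change is safer than relative change here, because a symptom score of zero at the start of a period would make a ratio undefined.
3. Keep the global-improvement VAS as a rating at Switch and month 12, with recall limited to the period just ended. It needs no Inclusion value.
4. For children without an Inclusion score, report symptom change as uncontrolled pre-post and say so.

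**Cost.** A few minutes of questionnaire at an existing visit and a small amendment. Data will be incomplete for children already included. Trial status describes recruitment as ongoing but expected it to end in March 2018, before the article appeared in June 2018, so the change may reach few patients and item 4 may carry most of the weight. Expectation bias from the open-label design remains.
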